#### 7.1.4 Females of childbearing potential

Females of childbearing potential must use contraception throughout the study period and for up to 180 days after the last dose of study therapy. Additionally, a pregnancy test (beta-human chorionic gonadotropin; beta-hCG) will be done monthly.

### 7.1.5 Study duration

The study duration for the individual participant will be approximately 20 weeks: 5 weeks of standard neoadjuvant CRT, following surgery 10 to 12 weeks after, including routine clinical and diagnostic work up of about 3 weeks.

### 7.1.6 Withdrawal and replacement of subjects

#### Criteria for withdrawal

Subjects may prematurely discontinue from the study at any time. Premature discontinuation from the study means that the subject did not undergo an end of study (EOS) examination as planned per protocol.

Subjects must be withdrawn under the following circumstances:

- at their own request
- if the Investigator feels it would not be in the best interest of the subject to continue
- if the subject violates conditions laid out in the consent form / information sheet or disregards instructions by the study personal
- in case of unacceptable toxicity
- in case of pregnancy of the subject
- if the entire study is terminated for medical or ethical reasons

In all cases, the reason why subjects are withdrawn must be recorded in detail in the eCRF and in the subject's medical records. Should the study be discontinued prematurely, all study materials (completed, partially completed and empty eCRFs) will be retained.

#### Follow-up of patients withdrawn from the study

In case of premature discontinuation after study drug intake, the investigations scheduled for the EOS visit will be performed 28 days after study drug discontinuation. The subjects will be advised that participation in these investigations is voluntary. Furthermore, they may request that from the time point of withdrawal no more data will be recorded and that all biological samples collected in the course of the study will be destroyed.

#### Replacement policy

Patients who discontinue the clinical trial before receiving the first cycle of treatment will be replaced. All other drop-outs will be included in the sample size.

### 7.1.7 Premature termination of the study

The sponsor has the right to close this study at any time. The IEC and the competent regulatory authority must be informed within 15 days of early termination.

The trial or single dose steps will be terminated prematurely in the following cases:

- If adverse events occur which are so serious that the risk-benefit ratio is not acceptable.
- If the number of dropouts is so high that proper completion of the trial cannot realistically be expected.

## 8 METHODOLOGY

### 8.1 Application of standard neoadjuvant CRT

Standard neoadjuvant CRT will be given according to the latest ESMO guidelines [3]. Briefly, a total of 50 Gy will be applied in 2 Gy fractions with Capecitabine 1650 mg/m^2/d over 25 working days (Monday to Friday). Radiation will be delivered by 3D conformal techniques, such as intensity-modulated radiotherapy (IMRT) or volumetric-modulated arc therapy (VMAT).

### 8.2 Study medications

#### 8.2.1 Investigational medicinal products (IMPs)

**Active agent and characteristics:** Ipilimumab

**Trade name of the agent:** Yervoy®

**Manufacturer:** Bristol-Myers Squibb

**Drug supply:** Ipilimumab is supplied as a Clear to slightly opalescent, colorless to pale yellow liquid and has a pH of 7.0 and an osmolality of 260-300 mOsm/kg. Each ml of concentrate contains 5 mg ipilimumab. Excipients are tris hydrochloride, sodium chloride, mannitol, pentetic acid, polysorbate 80, sodium hydroxide, hydrochloric acid and water for injections.

**Storage Instructions:** Store in a refrigerator (2°C to 8°C). Do not freeze. Store in the original package in order to protect from light. From a microbiological point of view, once opened, the medicinal product should be infused or diluted and infused immediately. The chemical and physical in-use stability of the undiluted or diluted concentrate (between 1 and 4 mg/ml) has been demonstrated for 24 h at 25°C and 2°C to 8°C. If not used immediately, the infusion solution (undiluted or diluted) may be stored for up to 24 hours in a refrigerator (2°C to 8°C) or at room temperature (20°C to 25°C).

**Route of administration:** IV over 30 minutes

Further specifications can be found in the investigator's brochure (IB) for Ipilimumab (section 5.6).

**Active agent and characteristics:** Nivolumab

**Trade name of the agent:** Opdivo®

**Manufacturer:** Bristol-Myers Squibb

**Drug supply:** Nivolumab is supplied as a clear to opalescent, colorless to pale yellow liquid. The solution has a pH of approximately 6.0 and an osmolality of approximately 340 mOsm/kg. Each ml of concentrate contains 10 mg of nivolumab. Excipients are sodium citrate dihydrate, sodium chloride, mannitol, pentetic acid, polysorbate 80, sodium hydroxide, hydrochloric acid and water for injections.

**Storage Instructions:** Store in a refrigerator (2°C to 8°C). Do not freeze. Store in the original package in order to protect from light. From a microbiological point of view, the product should be used immediately. If not used immediately, chemical and physical in-use stability has been demonstrated for 24 h at 2°C to 8°C protected from light and a maximum of 8 h at 20°C to 25°C and room light (this 8-hour period of the total 24 h should be inclusive of the product administration period).

[figure not shown]

**Route of administration:** IV over 30 minutes

Further specifications can be found in the IB for nivolumab (section 5.6).

### 8.2.2 Standard of care (SOC) medication

**Active agent and characteristics:** Capecitabine

**Trade name of the agent:** generic

**Manufacturer:** generic

**Drug supply:** generic specific

**Storage Instructions:** generic specific

**Route of administration:** PO

Further specifications can be found in the generic specific SmPC.

### 8.2.3 Dosage and administration

**Initial dose:** Ipilimumab 1 mg/kg on day 7 during standard neoadjuvant CRT

**Maintenance dose:** N.A.

**Route of administration:** IV over 30 minutes

**Duration:** single dose

**Initial dose:** Nivolumab 3 mg/kg on day 14 during standard neoadjuvant CRT

**Maintenance dose:** 3 mg/kg

**Route of administration:** IV over 30 minutes

**Duration:** given every 2 weeks until day 42 (3 cycles in total)

**Initial dose:** Capecitabine 1650 mg/m^2/d given as two equal doses per day concurrent with standard neoadjuvant CRT

**Maintenance dose:** 1650 mg/m^2/d given as two equal doses per day

**Route of administration:** PO

**Duration:** given concurrent with standard neoadjuvant CRT over 25 working days

### 8.2.4 Study-drug up- and down titration

There will be no up and down titration or dose modifications of the investigational drugs.

### 8.2.5 Study drug interruption or discontinuation

The Investigator must temporarily interrupt or permanently discontinue the study drug according to the specifications in the drug specific SmPC.

The reason for study drug interruption or premature permanent discontinuation must be documented in the eCRF.

### 8.2.6 Study drug premature permanent discontinuation

#### **Study drug premature permanent discontinuation due to an adverse event**

If the reason for premature permanent discontinuation of study treatment is due to a specification in the drug specific SmPC, the patient should have a “Premature End of Study (EOS)” visit with all the assessments performed before the study drug discontinuation, whenever possible.

### 8.2.7 Study-drug delivery & drug storage conditions

The investigational drugs will be provided by Bristol-Myers Squibb and stored at the hospital pharmacies of the Vienna General Hospital (AKH) according to the storage conditions specified in the SmPC.

### 8.2.8 Study drug packaging and labeling

Investigational drugs will be provided and packed Bristol-Myers Squibb. Investigational drugs will be labeled by the institutional pharmacies of the trial centers.

### 8.2.9 IMP administration & handling

The investigational drugs will be administered and handled according to the specifications in the SmPC.

### 8.2.10 Drug accountability

The investigational drugs will be requested from the hospital pharmacies of the Vienna General Hospital (AKH) for each study participant separately and administered promptly. Drug dispensing will be documented by site staff.

### 8.2.11 Procedures to assess subject's compliance

Not applicable due to IV administration of the investigational drugs by medical personnel.

[figure not shown]

### 8.2.12 Concomitant medication

The use of systemic corticosteroids and other immunosuppressants at baseline, before starting nivolumab or ipilimumab, should be avoided because of their potential interference with the pharmacodynamic activity. However, systemic corticosteroids and other immunosuppressants can be used after starting nivolumab to treat immune-related adverse reactions. The preliminary results show that systemic immunosuppression after starting nivolumab treatment does not appear to preclude the response on nivolumab or ipilimumab.

The use of anticoagulants is known to increase the risk of gastrointestinal hemorrhage. Since gastrointestinal hemorrhage is an adverse reaction with ipilimumab, patients who require concomitant anticoagulant therapy should be monitored closely.

Any concomitant medication should be documented in the patient's records. The use of concomitant medications should follow standard medical oncology practice.

## 8.3 Surgery

Patients will be operated about 10-12 weeks post CRT. Surgical options included standard total mesorectal excision (TME) or extended TME (*i.e.* TME with adjacent visceral resection) with or without sphincter preservation (abdominoperineal excision; APE) according to a standardized technique [34][3]. Patients will receive either a minimal invasive (laparoscopic, laparoscopic-assisted or robotic) or an open approach, depending on the perioperative circumstances (*i.e.* body constitution and cardiopulmonary fitness of the patient) and the surgeon's choice and expertise.

## 8.4 Randomization and stratification

On day 0 patients will be randomized to 1 of the 2 study groups using a "permuted block randomization" with a block size of 8 (<https://www.meduniwien.ac.at/randomizer>).

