| DESIGN / PHASE           | Prospective randomized, open-label, multicenter, phase II clinical trial                                                                                                                                                                                                                                                                                                                                                                                                                                                                                                                                                                                                                                                                                                                                                                                                                                                                                                                                                                                                                                                                                                                 |                   |                                           |                   |                                          |                   |

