| PATIENTS / GROUPS        | 
80 patients, 2 groups (50 treatment arm, 30 control arm)
 
Randomization ratio 30:50
                                                                                                                                                                                                                                                                                                                                                                                                                                                                                                                                                                                                                                                                                                                                                                                                                                                                                                                                                                                                                                                                                  |                   |                                           |                   |                                          |                   |

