## 8.5 Blinding

Not applicable due to the open-label study design.

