#### 11.4.2 Primary endpoint analysis

Safety and tolerability will be assessed by comparing case numbers for any complication in the treatment arm (n=50) with the calculated 95% upper CI numbers of the calculated percentage of expected numbers of current standard therapy (Table 2). Case numbers in the control arm (n=30) will be used to validate expected numbers from current standard therapy (*i.e.* will be compared to the corresponding 95% CI lower and upper borders).

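### Section 8.4 fixes and prints a block size of 8 in an open-label 3:5 trial, so someone who sees every earlier assignment can know up to 21.9% of assignments in advance

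*Protocol*

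**What the plan says.** Under Protocol section 8.4, patients are, on day 0 and through a web randomiser, "randomized to 1 of the 2 study groups using a 'permuted block randomization' with a block size of 8". One size is given. Nothing there varies it or withholds it from recruiting staff, and the protocol is a document that investigators hold. The section heading mentions stratification, but the text names no factor and does not say whether there is one list or one per centre.

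The synopsis gives "80 patients, 2 groups (50 treatment arm, 30 control arm") and "Randomization ratio 30:50". It describes the trial as "Prospective randomized, open-label, multicenter, phase II clinical trial". Section 8.5 says of blinding: "Not applicable due to the open-label study design".

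The primary rule in section 11.4.2 works by "comparing case numbers for any complication in the treatment arm (n=50) with the calculated 95% upper CI numbers" derived from published rates. The control arm serves to check that those published rates apply. Section 11.4.5 leaves baseline parameters out of the safety and tolerability analyses.

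**The concern.** In an open-label trial, past assignments are visible to those treating the patients. If the block size is also known and never changes, the end of each block can be worked out by counting. A web randomiser hides the list but does not prevent this.

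The trial gives some reason to care:
- Section 8.6 expects a major benefit for treatment-arm patients, so recruiters may not be indifferent to the arm.
- Consent and eligibility are settled at screening (days -21 to -1), so the timing or order of randomisation is partly in the site's hands.
- Postoperative complications depend on fitness, much of which can be judged beforehand.
- With no baseline adjustment in the safety analyses, any imbalance in who enters the treatment arm would pass straight into the count on which the verdict rests.

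**Working it through.** **Inputs.** Block size 8 (section 8.4); ratio 30:50 and total 80 (synopsis). The split within a block is not written out. At 3:5, a block of 8 must hold 3 control and 5 treatment places.

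**Plan's own figure.** 80/8 = 10 blocks; 10 × 5 = 50 treatment and 10 × 3 = 30 control. This reproduces the stated arm sizes.

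**Certain assignments, all earlier assignments known.** An assignment is certain once one arm's places in the block are used up. For m and n places in random order, the expected number is m/(n+1) + n/(m+1):
- treatment: 5/(3+1) = 1.25
- control: 3/(5+1) = 0.50
- total: 1.75 per block; 1.75/8 = 21.9%; 10 × 1.75 = 17.5 of 80

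Enumerating the 56 possible orderings gives the same answer. The block ends with 1, 2, 3, 4 or 5 certain assignments in 30, 15, 7, 3 and 1 orderings: (30 + 30 + 21 + 12 + 5)/56 = 98/56 = 1.75. Every block ends with at least one.

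**Best guess.** Always naming the arm with more places left (ties count half) is right 70.8% of the time. Always naming treatment is right 5/8 = 62.5% of the time.

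**A site that sees only its own patients on one shared list.** The recruitment shares are assumptions. In the simulation an assignment counts as certain only if the site's own earlier patients already fill one arm of the block, and the site is granted knowledge of where blocks start.

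| Site's share of recruitment | Certain assignments |
|---|---|
| 100% | 21.9% |
| 75% | about 8% |
| 50% | about 2% |
| 25% | about 0.2% |

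**Effect on outcomes, illustration only.** Assume full tracking, with a patient's complication risk lower by d when the chance of treatment is above 5/8, higher by d when it is below, and unchanged when equal. Over the 56 orderings the shifts sum to -75d across 280 treatment places and +75d across 168 control places:
- treatment: -75/280 = -0.268d
- control: +75/168 = +0.446d
- difference: 0.714d

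With d = 10 points:
- treatment arm: 2.68 points lower × 50 = about 1.3 fewer cases
- control arm: 4.46 points higher × 30 = about 1.3 more cases
- between arms: about 7.1 points

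For scale, Table 2 at 22.5% has 11 expected cases and an upper bound of 18 in the treatment arm, and 7 expected with bounds 3 and 13 in the control arm.

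**Varying block sizes (simulated, 80 patients, sizes drawn at random, guesser knows the possible sizes).**

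| Sizes | Later block starts unknown | Block starts known |
|---|---|---|
| 8, 16 | about 5% | about 8% |
| 8, 16, 24 | about 2% | about 4% |

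A single known size of 16 would still leave (10/7 + 6/11)/16 = 12.3%.

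**The case against.** The strongest reply is that 21.9% is a ceiling. It needs knowledge of every earlier assignment in the block. If one list serves a multicentre trial, an individual site sees only part of it, and the share that it can know drops steeply. This stands, and the figure has to be stated with its condition.

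A reader might infer that the central pharmacy closes the gap, since "The investigational drugs will be requested from the hospital pharmacies of the Vienna General Hospital (AKH) for each study participant separately". It does so only in part. Control patients generate no request for investigational drug, so pharmacy requests show treatment-arm patients only. Counting down a block needs the control assignments too. The documents describe no other route by which a site would learn them, although coordinating staff could.

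There is also limited room to steer. The synopsis plans first visits from 1Q 2020 to 2Q 2022, roughly 24 to 30 months for 80 patients, or about 3 a month. With a three-week screening window, that is about two candidates at a time across all centres. A 10-point shift at every favourable place is therefore an assumption, not something derived from the protocol. Its direction is assumed too.

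Finally, a reader might take the 7-point gap as the bias in the primary verdict. It is not. The primary rule sets the treatment arm against published rates, where the same assumption moves the count by about 1.3 cases against a distance of 7 cases from expected to upper bound in Table 2.

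What remains is that the protocol discloses a fixed block size when it need not. Nothing in it limits what coordinating staff could deduce, or each centre if lists are per centre.

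**Conclusion.** The concern holds as an avoidable weakness in allocation concealment. Up to 21.9% of assignments (1.75 per block, up to 17.5 of 80) can be known in advance by someone who sees all earlier assignments in the block. That means coordinating staff, or each centre over full blocks if lists are per centre, which the protocol neither states nor excludes. A site with partial sight of one shared list would know about 8% or less at recruitment shares of 75% or below.

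The consequence is a possibility only. Nothing in the protocol shows that patients will be steered, and the point does not invalidate the trial or any of its planned calculations. On the illustrative assumption the primary count changes little (about 1.3 of 50). The between-arm secondary comparisons are more exposed (about 7 points). The point merits correction because the remedy is simple, not because the verdict is shown to be at risk.

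**What to change.** In section 8.4, replace the fixed size by wording such as: *permuted blocks of randomly varying size that keep the 3:5 ratio*. Hold the sizes in a document restricted to the randomisation administrator, outside the investigator protocol. Sizes 8 and 16 bring certain assignments down to about 5%, and sizes 8, 16 and 24 to about 2%, when later block starts are unknown (about 8% and 4% when they are known). State in the same sentence whether there is one list or one per centre.

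No change to the order of consent, eligibility and randomisation is needed, because Table 4 already places the first two at screening, before day 0.

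The cost is a protocol amendment handled under section 13.2.1, and a check that the randomiser in use supports varying sizes, which the documents do not say. The final split may differ slightly from 30:50 if the last block is incomplete. Choosing a block sequence that sums to 80 avoids this (for example four blocks of 16 and two of 8: 64 + 16 = 80), provided its order is random and kept undisclosed.

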## 8.5 Blinding

Not applicable due to the open-label study design.

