## 6 STUDY OBJECTIVES

### 6.1 Primary objective

- Safety, tolerability and feasibility of sequential neoadjuvant ipilimumab and nivolumab in combination with standard neoadjuvant CRT, following surgical resection, assessed by the latest “Clavien-Dindo Classification of surgical complications” [26] (see section 9.1.2 ) and Common Terminology Criteria of Adverse Events (CTCAE) [27] (see section 9.4 ).

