### 6.2 Secondary objectives

- Radiographic response determined by magnetic resonance imaging-assessed tumor regression grade (mrTRG) [28]:
  - mrTRG 1 (no evidence of ever treated tumor)
  - mrTRG 2 (good response: dense fibrosis no obvious residual tumor)
  - mrTRG 3 (moderate response: >50% fibrosis or mucin & visible intermediate signal)
  - mrTRG 4 (slight response: little areas of fibrosis or mucin, but mostly tumor)
  - mrTRG 5 (no response)
- Pathological therapy response determined by tumor regression grade (TRG) [29]–[32] and the latest American Joint Committee on Cancer/International Union Against Cancer-Tumor Node Metastasis (AJCC/UICC-TNM) tumor stage [33].  
TRG according to Dworak *et al.* [32]:
  - TRG 0 (no regression)
  - TRG 1 (predominantly tumor with significant fibrosis and/or vasculopathy)
  - TRG 2 (predominantly fibrosis with scattered tumor cells)
  - TRG 3 (only scattered tumor cells in the space of fibrosis with/without acellular mucin)
  - TRG 4 (no vital tumor cells detectable)
- Correlate genomic information (*i.e.* MSI, KRAS, BRAF, TP53, PTEN, PIK3CA, TMB, *etc.*) with pathological and radiographic therapy response.
- Correlate genomic, transcriptomic, epigenomic and/or proteomic pattern of liquid biopsies (serum, plasma, PBMCs) taken on day -21 to -1, 7, 14, 28, 42, before surgery and at the EOSV with therapy response and clinical outcome.
- Correlate genomic, transcriptomic, epigenomic and/or proteomic pattern of tumor biopsies taken on day -21 to -1, 14 and 28 with therapy response and clinical outcome.
- Correlate immune infiltrate of resected specimen with therapy response

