## 8.6 Benefit and risk assessment

As this study is primarily designed for the assessment of safety, tolerability and feasibility of a single dose of neoadjuvant ipilimumab and following 3 cycles of nivolumab in combination with standard neoadjuvant CRT in rectal cancer, there is no explicit benefit for the individual participant. Other interventions, such as blood drawing, tumor biopsies, computed tomography (CT), magnetic resonance imaging (MRI), positron-emission tomography (PET), neoadjuvant CRT, following surgical resection are standard care of treatment for rectal cancer patients. However, it is expected that patients within the treatment arm are going to have a major benefit in terms of pathological response and consequently clinical outcome.

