#### 11.4.3 Secondary endpoint analysis

Statistical analysis of secondary objectives, especially between control and treatment arm will be performed according the nature of the outcome parameter. Nominal and dichotomous, outcomes will be compared by Chi-squared or Fisher's exact tests, continuous variables will be compared by T-tests (after  $\log_2$  transformation) or by Mann-Whitney-U tests and censored survival outcomes by Cox-regression analysis. Potential confounders will be considered in corresponding statistical models. Multiple testing will be corrected for by the Holm's Step-Down method or by the false discovery rate (FDR) method after Benjamini-Hochberg (especially omics data) [42]. Adjusted p-values (q-values) below 0.05 will be considered as statistically significant.

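### Section 8.5 rules out all blinding because dosing is open-label, so nothing keeps the readers of the MRI and pathology response grades from knowing the arm

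*Protocol*

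**What the plan says.** The synopsis describes the trial as a "Prospective randomized, open-label, multicenter, phase II clinical trial". Section 8.5 (Blinding) consists of the statement "Not applicable due to the open-label study design", and the two subsections on emergency and end-of-study unblinding repeat it. No section provides for masked, central or independent reading of images or specimens.

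Section 6.1 makes safety, tolerability and feasibility the primary objective. Section 6.2 lists as the first two secondary objectives the radiographic response (mrTRG, grades 1 to 5) and the pathological response (Dworak TRG, grades 0 to 4, with tumour stage). Table 4 schedules the post-treatment pelvic MRI at week 15 and surgery at weeks 15 to 17.

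Section 11.4.3 opens with "Statistical analysis of secondary objectives, especially between control and treatment arm" and sets significance at an adjusted p-value below 0.05. Section 8.6 says that "it is expected that patients within the treatment arm are going to have a major benefit in terms of pathological response".

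**The concern.** Whether dosing is open and whether an outcome is read open are separate decisions. A patient receiving infusions cannot be masked, but a scan or a slide can be graded by someone who has not been told the arm. Section 8.5 gives a reason that fits the first decision and uses it to close the second.

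This matters because both regression scales are ordinal visual judgements. Neighbouring grades are separated by the reader's impression of how much fibrosis and how much residual tumour is present. If knowledge of the arm moves borderline cases in one direction in one arm, the between-arm response comparison is biased. The same grades are the response variable for the genomic, biopsy and immune-infiltrate correlations in section 6.2, so a correlation that pools the arms without adjusting for arm could also be affected.

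Masking of readers is a matter of trial conduct and belongs in the protocol. A separate analysis plan cannot mask a reading that has already been made.

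**Working it through.** **Step 1. The provisions side by side.**
- Section 8.5: no blinding, and the only reason given is open-label treatment.
- Section 6.2: two visually graded response scales.
- Section 11.4.3: secondary outcomes compared between arms, adjusted p below 0.05.
- Section 8.6: a stated direction of expectation on pathological response.
- Sections 8.3, 8.7.2, 8.7.5 and 11: nothing on who assigns the grades or what they know.

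The reason in 8.5 does not reach the readers, and nothing elsewhere fills the gap.

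**Step 2. The protocol's own figure.** The protocol gives no planning figure for response. Its one power statement (section 11.2: 49 patients, 23% against 46%) concerns surgical complications and plays no part here.

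**Step 3. What arm-dependent grading could do (illustration).** From the protocol: 50 treatment and 30 control patients. Assumed, because the documents give no response rates:
- Dworak TRG 0/1/2/3/4 in 5/20/35/25/15% of both arms, so there is no true effect.
- A share b of treatment-arm specimens read one grade higher, capped at TRG 4.
- Two-sided Mann-Whitney test, with the rejection rate found by simulation.

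| b | Rejects at 0.05 | Rejects at 0.025 |
|---|---|---|
| 0% | about 5% | about 2% |
| 10% | about 6% | about 3% |
| 20% | about 10% | about 6% |
| 30% | about 17% | about 10% |

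The 0.025 column is the strictest Holm step if only two endpoints are in the family. It shows how far the multiplicity correction in section 11.4.3 would lower these rates.

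**Step 4. The same question for complete response (TRG 4).** If a share s of TRG 3 specimens in the treatment arm is read as TRG 4, the apparent rate is 15% + 25% × s.
- s = 20%: 15% + 5% = 20%. Fisher's exact test against a control rate of 15% rejects in about 6% of trials.
- s = 40%: 15% + 10% = 25%. It rejects in about 14%.
- With no misreading it rejects in about 4%.

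**Step 5. A different model as a check.** Take a good-response rate q of 20% to 40% in both arms, with a share b of true non-responders upgraded in the treatment arm only. The apparent rate is q + (1 − q) × b. For example, q = 20% and b = 10% gives 20% + 80% × 10% = 28%. Exact rejection rates of an unadjusted two-sided 5% Fisher test:

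| b | q = 20% | q = 30% | q = 40% |
|---|---|---|---|
| 0% | 3.4% | 3.8% | 3.6% |
| 10% | 9.3% | 7.6% | 6.4% |
| 20% | 28.9% | 19.9% | 15.1% |
| 30% | 56.1% | 41.0% | 29.9% |

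The direction agrees with step 3. The size depends strongly on how the misreading is modelled.

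**The case against.** **Do the readers know the arm?** A reader might infer from 8.5 that the grades will be read with the arm known, by people who expect a benefit. The documents do not support that. They do not say who reads the MRI or the specimen, or that these readers are told the arm. The expectation in 8.6 is the protocol's own statement in a benefit-risk section and is not attributed to any reader. The unblinding subsections also suggest that 8.5 was written with treatment blinding in mind. This objection stands: the supportable claim is only that nothing prevents the readers from knowing.

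**Is the main conclusion at risk?** No. The primary analysis (section 11.4.2) compares complication counts with confidence limits, and the stopping rule (section 11.4.6) counts reoperations. Neither uses mrTRG or TRG.

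**Is the bias irreversible?** One might conclude so, but the documents point the other way. Section 8.7.5 provides for biobanking of resected tissue and whole-slide scanning of stained sections, and pelvic MRI is a scheduled assessment. If the material is kept, a masked re-read could produce fresh grades. It would be later and dearer than masking the first read.

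**Would every biomarker correlation be distorted?** That is too broad. A spurious association needs pooled arms, no adjustment for arm, and a biomarker that differs by arm. Within an arm, upgrading unrelated to the biomarker would tend to weaken an association. Section 11.4.3 says confounders will be considered, and some correlations use clinical outcome as well as response.

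**Are the error rates realistic?** They show sensitivity to a hypothetical bias and do not forecast one. The distributions and upgrade shares have no source in the documents. At a 10% upgrade the rank-test effect is only about one percentage point.

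**Conclusion.** The point holds for the secondary response endpoints. Section 8.5 excludes masked reading for a reason that does not apply to it, and the grades left unprotected are judgement-based, compared between arms and reused as the response variable in the correlative work. The absence of any masking provision is certain on the documents. Whether readers would know the arm, and whether that would change their grades, is not.

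The size is conditional. Under step 3's assumptions, the false-positive rate of a nominal 5% test rises to about 6% to 17% when 10% to 30% of treatment-arm specimens are upgraded, and less after multiplicity correction. The dichotomised model in step 5 gives larger rates. The point is worth correcting because prevention is cheap.

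**What to change.** Reword section 8.5 to separate treatment from assessment: treatment is open-label, but the study mrTRG and the pathological TRG, ypT and ypN are assigned by the existing readers without knowledge of study arm and entered in the eCRF before allocation is disclosed to the reader.

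Limit the masking to the study grade. The week-15 MRI precedes surgery, so clinical information needed for the routine diagnostic report should stay available once the study grade is recorded.

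The cost is the wording and some administrative handling of requests and the order of eCRF entry. It needs no extra readers, reads, patients or procedures, and it changes no sample size or significance level. Masking may be imperfect where hospital records or the tissue itself reveal the arm.
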